### Power and sample size

Herein, the major endpoint is the percentage of patients whose hypotension is restituted within 6 hours. According to the study by Permpikul C, et al (the CENSOR trial [5]), the shock control rate at 6 hours was significantly higher in the early norepinephrine group (76.1%) versus (48.4%) in the Placebo group. Consequently, the computation is performed as follows:

N per group = x

Where pA is the percentage of shock control within 6 hours in the early norepinephrine group (0.761) and pB is the percentage in the placebo group (0.484). Thus, for a targeted statistical power of at least 90% and at an alpha risk of 0.05, the size required for each arm is at least 96 patients. The desired effect size, based on the power and sample size mentioned above, was estimated at a gain of 1 hour 45 minutes from initial treatment to achieving target MAP and tissue perfusion goal.

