## Materials and methods

### Trial design

This is a multicenter parallel-group, randomized, interventional, active controlled trial. The 1:1 allocation ratio is regularly checked.

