### Statistical analyses planned

Enrollment of at least 96 participants per group would provide a statistical power at 90% to assess the difference in the primary outcome between the two groups at a two-sided alpha error of 0.05. All primary and secondary outcomes analyses are based on the intention-to-treat principle. The primary outcome and other categorical variables are evaluated by the chi-square test or Fisher exact test, where appropriate. The independent link between early NE and shock resolution will be evaluated using proportion regression (Beta regression approach). Under violations of normality/Gaussian assumptions, we will employ the Wilcoxon-Mann-Whitney test to assess group differences for continuous variables. For the 28-day mortality analysis, time to death is calculated from date of sepsis diagnosis to date of death. Survival distributions in the two groups are estimated by Kaplan-Meier curves. Values of p less than 0.05 are considered to indicate statistical significance. All data analyses will be performed using SPSS Statistics version 20 (SPSS Inc.). Missing data will be handled using the imputation approach.

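### The stated inputs need about 63 patients per arm, not 96, and the 1 h 45 min effect size has no basis in the calculation shown

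*Protocol article*

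**What the plan says.** The Power and sample size section of the protocol article borrows the shock-control rates of an earlier single-centre trial: pA = 0.761 with early norepinephrine and pB = 0.484 with placebo. It sets the target as "for a targeted statistical power of at least 90" (per cent) and concludes that "at an alpha risk of 0.05, the size required for each arm is at least 96 patients".

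The section Statistical analyses planned repeats the result without the words at least: "Enrollment of at least 96 participants per group would provide a statistical power at 90" (per cent). It adds that the test is run "at a two-sided alpha error of 0.05", using chi-square or Fisher's exact test. Trial design gives equal allocation. The Abstract and the Discussion give a target of at least 100 per group.

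The Power and sample size section ends with a second effect size, presented as resting on the same power and sample size. It "was estimated at a gain of 1 hour 45 minutes from initial treatment to achieving target MAP" and the tissue perfusion goal.

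**The concern.** A stated sample size should follow from its stated inputs. Here every input is given: two proportions, alpha, sidedness, power and allocation. Yet 96 is well above what they require. A reader cannot tell whether 96 contains an undeclared allowance, was set for a higher power, or is a slip, and so cannot tell what difference the trial can detect with 90% power.

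The time figure is a separate fault. It gives the trial a second design target, in hours, that the calculation shown cannot produce. It could later be quoted as the difference the trial was built to detect.

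**Working it through.** **Inputs.** pA = 0.761 and pB = 0.484, so the difference is 0.277; alpha 0.05; power 90% (Power and sample size). Two-sided, chi-square or Fisher (Statistical analyses planned). 1:1 allocation (Trial design). The printed formula did not survive text extraction. That is no fault of the plan, and standard formulas are used here.

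**Attempt to reproduce 96.** With p̄ = (0.761 + 0.484)/2 = 0.6225,

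n = [1.96·√(2·0.6225·0.3775) + 1.2816·√(0.761·0.239 + 0.484·0.516)]² / 0.277²

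= [1.96·0.6856 + 1.2816·0.6570]² / 0.0767 = 4.777/0.0767 = 62.3, so **63 per arm**.

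With the continuity correction, n' = (n/4)·[1 + √(1 + 4/(n·0.277))]² = 69.3, so **70 per arm**. Exact enumeration shows that 70 per arm also suffices for Fisher's test (power 90.4%).

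| Variant (two-sided 0.05, 90% power) | n per arm |
|---|---|
| Unpooled variance | 60 |
| Pooled/unpooled formula above | 63 |
| Arcsine | 63 |
| Simple pooled variance | 65 |
| Continuity-corrected | 70 |
| **Stated in the article** | **96** |

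One-sided testing lowers the requirement further, to 49 to 58. The stated 96 is 52% above 63 (96/63 = 1.52) and 37% above 70 (96/70 = 1.37).

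**Power at 96 per arm.** z = (0.277·√96 − 1.3437)/0.6570 = (2.7140 − 1.3437)/0.6570 = 2.086, which gives 98.2%. Exact enumeration gives 98.1% for the chi-square test and 97.3% for Fisher's test. At 100 per arm, z = (2.77 − 1.3437)/0.6570 = 2.171, which gives 98.5%.

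**Difference detectable with 90% power.** Hold the control rate at 48.4% and solve the same formula for the other rate. At 96 per arm it is 71.1%, a difference of 22.7 points. At 100 per arm it is 70.7%, a difference of 22.3 points.

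**Allowance needed to reach 96.** If loss alone explains it: 1 − 63/96 = 34%, or 1 − 70/96 = 27% from the corrected figure. If clustering alone explains it, the design effect would be 96/63 = 1.52. The article states neither.

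**The time figure.** The calculation uses two proportions, alpha and power. A gain in hours would need a standard deviation, a time distribution, a hazard or an event count, and none is given. The Outcomes section lists no time to shock control, and the statistical section describes survival methods only for 28-day mortality. Studied variables does record when the haemodynamic objective is reached, so the data will exist, but no outcome or calculation uses them.

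**The case against.** The strongest defence is that nothing is too small. The target is worded as at least 90% power and at least 96 patients, and 98% satisfies the first. This stands: a reader might infer that the planned power is inadequate or that enrolment must change, and the documents support neither. The 27.7-point effect is also carried over correctly from the cited rates. What fails is narrower. The Power section calls 96 the size required, and the statistical section says flatly that 96 gives 90%.

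Second, the formula is not visible, this is a condensed article, and the Discussion says that correlation from the multicentre design must be controlled. An allowance may therefore sit in the full protocol. That also stands, so an arithmetic slip is not proven. But the Discussion does not tie centre correlation to the sample size, and the article presents 96 as following directly from the inputs it lists.

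Third, a reader who searches for inputs that give 96 might infer a hidden alpha of 0.01, since 90% power with a continuity correction then gives 95.7. The documents do not support that. At the stated alpha of 0.05, 98% power gives 95 per arm, and 95% power with 20% attrition gives 76.6/0.8 = 95.7. Several routes lead to about 96, and each needs something the article does not state.

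Fourth, because the Power section opens by speaking of restored hypotension, a reader might infer that the wrong endpoint was sized. The same section defines its terms as shock control: "pA is the percentage of shock control within 6 hours in the early norepinephrine group (0.761". That is the name of the primary outcome, so the opening phrase is only loose wording.

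Finally, what a null result excludes will be read from its confidence interval rather than from planning power, which limits the practical harm.

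**Conclusion.** The point holds in this limited form. On the stated inputs, 90% power needs about 63 per arm (60 to 70 across standard two-sided methods), and 96 per arm gives about 98%, some 8 points above the figure in the statistical section. The description of 96 as required and the flat 90% are wrong as written unless an undeclared allowance lies behind them. The discrepancy is conservative and does not threaten the trial's power under its own assumptions.

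The 1 h 45 min effect size cannot come from the calculation it is attributed to and matches no listed outcome.

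The 98% figure assumes that all 96 per arm are evaluable, that patients are independent across centres, and that the borrowed rates apply. If 96 already includes a loss or clustering allowance, power should be worked out from the evaluable or effective number instead.

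**What to change.** Keep the enrolment target. Amend Power and sample size and Statistical analyses planned together, so that they give the same account:

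- If an allowance for loss or clustering leads to 96, declare it and state the power for the evaluable number.
- If there is none, restate along these lines: *96 per arm gives about 98% power for 76.1% vs 48.4%, or 90% power for a difference of about 22.7 points (48.4% vs 71.1%), chi-square test, two-sided alpha 0.05.*
- Delete the 1 h 45 min sentence, or give it its own stated source and calculation.

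The sponsor should be asked about the allowance first, because the restated wording would be wrong if 96 is an inflated number. The cost is wording only: no change to enrolment, outcomes or data collection.

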### Interim analyses and stopping guidelines

Not applicable.

### Randomization (random number generation, allocation concealment, implementation)

Once included, patients are randomized according to a succession of six blocks of random permutations block 1: NE (norepinephrine)- P (placebo)-NE-P, block 2: P-NE-P-NE, block 3: NE-NE-P-P, block 4: P-P-NE-NE, block 5: P-NE-NE-P, block 6: NE-P-P-NE. Randomization is achieved via a computer-generated program, which also stratified patients based on age (≤ 55 years versus > 55 years), and SrOFA score (≤5 versus >5). The program of patient allocation is managed by a statistician blinded to the trial process.

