### Blinding

The trial drug (early NE) is not disclosed to the patient, as per the single-blind protocol.

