## Discussion

In this multicenter RCT, we plan to include at least 200 patients (n = 100 per group), which is, to our knowledge, the first and largest RCT involving almost all Tunisian ICUs reported to date. During the preparation of this manuscript, the methodology diffusion via several meetings between the investigators is taking place. We plan to close the study inclusion in September 2024.

The trial’s methodology requires a certain level of attention; particularly during the first six hours. Indeed, during this time interval, the patient is enrolled in his trial group, basic data (hemodynamic parameters, echocardiography and lactate level) are collected, quantity of volume expansion is determined (while being guided by responsiveness indices and monitored by hourly intakes of MAP, diuresis, heart rate, skin recoloration time, etc…), labeling a success or failure status according to the defined endpoint composite criterion. This entire assessment will be redone at H6 in order to assess the effect of the tested action (early NE or standard care) on the stroke volume, cardiac output, LV filling pressures and on the drop in lactate. The received fluids volume over the 6 hours and the total cumulative dose of NE administered during the septic episode will be also quantified.

Concerning the fluid balance, it is now well established that a positive balance is independently associated with an increased mortality rate in septic shock [9, 10]. It makes perfect sense to restrict fluid intake by initiating vasopressors early. In fact, the CENSER-RCT [6] found that the shock was more resolved by 6 hours in the early norepinephrine group (118/155 [76.1%] vs. 75/155 [48.4%]; *P* < 0.001); yet the 28-day mortality did not differ [5]. Despite the large sample size (n = 155 per arm), this trial only included one center and did not evaluate the immediate impact on stroke volume and CO. In the current trial, we try to circumvent these two limitations.

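### A published constant block size of four and a numbered block list, with only the patient blinded, put allocation concealment at risk

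*Protocol article*

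**What the plan says.** The Randomization section of the protocol article states that "patients are randomized according to a succession of six blocks of random permutations". It prints blocks 1 to 3 as NE-P-NE-P, P-NE-P-NE and NE-NE-P-P, and continues: "block 4: P-P-NE-NE, block 5: P-NE-NE-P, block 6: NE-P-P-NE". It adds: "Randomization is achieved via a computer-generated program, which also stratified patients based on age" (cut at 55 years) and SOFA score (cut at 5), which makes four strata. Centre is not named as a stratum. On who holds the list, it states: "The program of patient allocation is managed by a statistician blinded to the trial process". Randomization takes place after inclusion.

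The Blinding section states: "The trial drug (early NE) is not disclosed to the patient, as per the single-blind protocol". No section says that the treating clinician is masked. The Interventions section describes a glucose preparation for the placebo group, but also says that this arm gets only the classic regimen.

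The Abstract calls the study ongoing, and the Discussion states: "We plan to close the study inclusion in September 2024". Eleven ICUs take part and at least 200 patients are planned.

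**The concern.** Permuted blocks protect against prediction only while their size and order stay unknown to those who enrol. Here the size is constant, the contents are printed and numbered, and the natural inference from a single-blind design is that clinicians know each past assignment. Someone with that knowledge can work out some or all of the next assignments.

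Foreknowledge does harm only where there is room to act on it, and this trial has such room. Under the eligibility criteria the infection may be merely suspected, and the exclusion for conditions that call for fluid restriction is open-ended. The Discussion recommends including patients only when a senior is present and during laboratory hours, and accepts that some eligible patients will be missed. A clinician who expects a given arm could delay, skip or favour a patient without breaking any written rule. Selection of this kind happens before randomization, so analysing everyone as randomized does not remove it. Selection on severity or renal function would bear directly on the primary outcome, half of which is urine output.

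**Working it through.** The plan gives no figure for predictability, so there is none to reproduce. The inputs are the six printed blocks, four strata, 11 centres and at least 200 patients.

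**1. What the list is.** Two NE and two P can be arranged in 4!/(2!·2!) = 6 ways. The six printed blocks are exactly these six. The list therefore fits two readings: the order of use, or the pool from which a program draws. It holds 6 × 4 = 24 assignments. With equal strata (an assumption), 200/4 = 50 patients fall in each stratum, so the 24 must be repeated or redrawn. The article does not say which.

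**2. Printed order used.** From a known start, 24 of 24 assignments are known in advance. If the sequence is cycled from an unknown start, matching runs of consecutive assignments against the 24-item cycle gives:

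| Consecutive assignments seen | Position uniquely located | Next arm certain |
|---|---|---|
| 4 | 8 of 24 | 17 of 24 |
| 9 | 24 of 24 | 24 of 24 |

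The next arm can be certain without the position being unique, because several matching positions may be followed by the same arm.

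**3. Blocks in random order, size four known, whole stratum seen.** The rule is to guess the arm with more places left in the block, and to toss a coin on a tie. Over the six equally likely blocks:

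| Place in block | Certain | Expected correct |
|---|---|---|
| 1 | 0 | 6 × 0.5 = 3 |
| 2 | 0 | 4 (four of six blocks switch arm) |
| 3 | 2 (after NE-NE or P-P) | 2 + 4 × 0.5 = 4 |
| 4 | 6 | 6 |
| Total | 8 of 24 = 33.3% | 17 of 24 = 70.8% |

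Chance is 50%.

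**4. Lists shared across centres.** With equal centres and strata (assumed), a centre sees 200/(11 × 4) ≈ 4.5 patients per stratum over the whole trial, and these are not consecutive on the list. A simulation used 200 patients, 11 equal centres, four strata, 2,000 runs and the rule of guessing the arm seen less often so far:

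| Design | Observer of whole stratum | Observer of one centre |
|---|---|---|
| Blocks of 4, random order | 70.5% | 51.3% |
| Hidden sizes 4, 6, 8, random order | 67.6% | 51.2% |

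The 70.5% agrees with the exact 70.8% up to incomplete final blocks and simulation error.

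**5. Lists held per centre.** A local clinician then sees the whole of each list, so steps 2 and 3 apply to that clinician, although each list is short.

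**The case against.** A reader might infer that the printed blocks are the actual sequence, repeated in order, and that concealment has therefore failed. The article does not support either step.

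- **Order.** The text also speaks of random permutations and of a computer program, and the list is the complete set of possible blocks. A methods section could list the pool in this way. The word for succession and the numbering permit the literal reading but do not prove it.
- **Safeguards.** Patients are randomized after inclusion, and the program is managed by a statistician kept apart from the trial process. Both count towards concealment. How an assignment reaches the bedside is a detail that an article may leave to the full protocol, so its absence is not held against the plan.
- **The observer.** The figures of 33% and 71% need someone who follows a whole list. Centre is not a named stratum, which points to shared lists. On such lists, with random block order, a single-centre clinician gains almost nothing. The average centre would also be unlikely to see nine consecutive assignments in one stratum.
- **Clinician knowledge.** That clinicians know the arm is inferred from the single-blind statement and is not itself stated.

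These points limit the claim but do not remove it. Keeping the list with an outside statistician does not stop others from inferring it once its size and contents are public. The article does not say that lists are shared. If the printed order was in fact used, anyone who can place a patient in it can read off what follows. Disclosing the scheme gains nothing for the trial.

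**Conclusion.** The point holds as a risk to concealment, not as a demonstrated failure. The documents establish a constant block size of four, printed and numbered block contents, blinding of the patient alone, and a study described as ongoing. They leave open whether the printed order is the order of use and whether lists are per centre, and the size turns on these two facts:

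- all assignments known, if the printed order is used from a known start;
- 33% certain and 71% guessed correctly, if the order is random and the observer sees the whole list;
- about 51%, if lists are shared, the order is random and the observer sees one centre.

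The last figure assumes equal centres and equal strata. All the figures assume that the enrolling clinician knows past assignments. None of them measures bias in the treatment effect: that would also need clinicians to act on the foreknowledge, and the documents are silent on this.

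**What to change.** For all remaining patients, the allocating statistician should generate a new list for each age by SOFA stratum, with randomly ordered blocks of randomly varying size. Blocks of two should be avoided, because their second place is certain once the size is known. Sizes 4, 6 and 8 serve here as an example; the set actually used, and the sequence, should stay out of site documents and publications.

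The authors should also state whether the printed order was actually used and whether lists are per centre or shared, and report the date of the switch with baseline balance before and after it. If enrolment has closed, the actual procedure and the baseline balance should still be reported.

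The expected gain should not be oversold. For a whole-stratum observer the rate of correct guesses falls only from 70.5% to 67.6%, and for a single-centre observer on shared lists it hardly moves. The main benefit is that assignments can no longer be known for certain. The cost is a short amendment, regeneration of the list in the existing program, and slightly looser balance within strata.

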### Blinding

The trial drug (early NE) is not disclosed to the patient, as per the single-blind protocol.

### Statistical analyses planned

Enrollment of at least 96 participants per group would provide a statistical power at 90% to assess the difference in the primary outcome between the two groups at a two-sided alpha error of 0.05. All primary and secondary outcomes analyses are based on the intention-to-treat principle. The primary outcome and other categorical variables are evaluated by the chi-square test or Fisher exact test, where appropriate. The independent link between early NE and shock resolution will be evaluated using proportion regression (Beta regression approach). Under violations of normality/Gaussian assumptions, we will employ the Wilcoxon-Mann-Whitney test to assess group differences for continuous variables. For the 28-day mortality analysis, time to death is calculated from date of sepsis diagnosis to date of death. Survival distributions in the two groups are estimated by Kaplan-Meier curves. Values of p less than 0.05 are considered to indicate statistical significance. All data analyses will be performed using SPSS Statistics version 20 (SPSS Inc.). Missing data will be handled using the imputation approach.

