### Participants, eligibility criteria, and settings

The study is conducted in 11 Tunisian medical ICUs: Rabta, Ariana, severe burns department, Zaghouan, Habib Thameur Center, Mahdia, Farhat Hached Sousse Center, Sfax, Bizerte, Tunis Urgent Medical Assistance Center, and Mahres. The recruitment period for this study is scheduled to begin on September 15, 2023 and end over one year, i.e. September 15, 2024. Are eligible for our trial, all patients aging 18 or older, admitted in ICU, who present sepsis and a decrease in MAP below 65 mmHg. According to the sepsis 3 definitions update [1], sepsis is defined as an organ dysfunction caused by a documented or suspected infection. Organ dysfunction is represented by an increase in the Sequential [sepsis-related] Organ Failure Assessment (SOFA) score of 2 points or more. Exclusion criteria are: pregnancy, surgery indication, neoplasia, circumstances where fluid restriction is the rule (acute cardiogenic pulmonary edema…).

It should be noted that sepsis is only considered for inclusion when it occurred in the ICU to minimize the interventional bias. Septic patients who started receiving fluid therapy or vasopressive agents in their original departments (emergency or others) are excluded. Patients who die before primary outcome assessment are considered treatment failure.

In accordance with ethical principles of international guidelines including the Declaration of Helsinki, Council for International Organizations of Medical Sciences (CIOMS) International Ethical Guidelines, and International Conference on Harmonization (ICH) Good Clinical Practice (GCP) Guidelines, the protocol and other relevant documents are reviewed and approved by the institutional ethics Committee of the Northern Data Protection Committee of Tunisia on 11/04/2023 (CPP_37_2022_SI_noradrénaline) (supplement document). A written and informed consent is obtained from all patients or their legal representative. In case of urgent inclusion, we opt to call the legal parents to find out who can provide oral consent—or not; after explaining the study and its objectives. If oral consent is provided, the written consent will be completed the next day.

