### Studied variables

Multiple and repeated measures are incorporated in the study design to ensure data integrity.

**At baseline:** clinical data related to the patient and septic state, hemodynamic status (in particular MAP, diuresis), biological data (blood gases with lactate), echocardiography parameters (stroke volume (SV), cardiac output (CO) and E/E’ ratio), hourly monitoring of MAP and urine output for 6 hours, hemodynamic objective achieved or not? and when? **At H6:** blood gases (P/F ratio and lactates) plus echocardiography parameters, quantity of fluids received over 6 hours. **Evolutionary parameters:** mortality, ventilation, hemodialysis, length of stay, etc.Note that all details of the EA-NE-S-TUN schedule of the study protocol are displayed in **Fig 1**.

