### Outcomes (primary and secondary)

Our Primary Outcome is the shock control defined by a composite criterion (MAP > 65 mm Hg for 2 consecutive measurements AND urinary output > 0.5 ml/kg/h for 2 consecutive hours) within 6 hours. Secondary Outcomes are: Variation of CO (the 15% threshold is considered to define an increase in CO) within 6 hours, decrease in serum lactate > 10% from baseline within 6 hours, Quantity of intravenous fluid received, Improvement of SOFA at H24, vasopressors free days, ICU stay, ventilator free days, and 28 days-Mortality.

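### The primary chi-square or Fisher test is valid but unadjusted, so it gives up modest precision that baseline MAP and urine output, already recorded, could supply

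*Protocol article*

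**What the plan says.** All of this is in the protocol article.

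- **Primary outcome** (Outcomes): a yes/no composite, "MAP > 65 mm Hg for 2 consecutive measurements AND urinary output > 0.5 ml/kg/h for 2 consecutive hours) within 6 hours".
- **Primary test** (Statistical analyses planned): "The primary outcome and other categorical variables are evaluated by the chi-square test or Fisher exact test, where appropriate".
- **Second analysis of the same outcome** (same section, next sentence): "The independent link between early NE and shock resolution will be evaluated using proportion regression (Beta regression approach". No covariates are listed.
- **Baseline data** (Studied variables): "hemodynamic status (in particular MAP, diuresis), biological data (blood gases with lactate".
- **Entry limit** (Participants, eligibility criteria, and settings): patients "who present sepsis and a decrease in MAP below 65 mmHg".
- **Planning rates** (Power and sample size): "pA is the percentage of shock control within 6 hours in the early norepinephrine group (0.761"; the placebo rate is taken as 0.484. The plan asks for at least 96 patients per arm for at least 90% power.
- **Design features** (Randomization; Discussion): allocation is stratified by age (cut at 55 years) and organ-failure score (cut at 5), and the Discussion calls control for multicentre correlation necessary.

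**The concern.** A patient's starting MAP and starting urine output are natural candidates to predict whether that patient meets thresholds on MAP and urine output within six hours. A two-by-two table uses neither. Where such values do predict the outcome, a treatment effect adjusted for them has a smaller standard error at the same sample size, without inflating the type I error.

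Stratified randomisation does not replace this adjustment. Age and organ-failure class do not fix the starting MAP or diuresis within a stratum.

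The regression in the following sentence does not clearly repair it either. It is not designated as the primary analysis, and it does not say what it adjusts for. Beta regression models a continuous proportion between 0 and 1, whereas each patient here contributes a success or a failure.

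At stake is the width of the confidence interval around the primary effect and, if the true effect is smaller than planned, some power.

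**Working it through.** **Step 1. The plan's own sample size.** Inputs from Power and sample size: pA = 0.761, pB = 0.484, difference d = 0.277, mean p̄ = 0.6225, two-sided alpha 0.05, power 90%.

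n = [1.960·√(2p̄(1−p̄)) + 1.282·√(pA(1−pA) + pB(1−pB))]² / d²

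= [1.960 × 0.6856 + 1.282 × 0.6570]² / 0.0767 ≈ 62.3, so 63 per arm, or 70 with continuity correction.

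The stated 96 is not reproduced. That is a separate matter, but it matters here because 96 is larger than the stated inputs require, so power has room to spare.

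**Step 2. Power of the unadjusted test at 96 per arm.**

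z = (d√n − 1.960·√(2p̄(1−p̄))) / √(pA(1−pA) + pB(1−pB))

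- Stated rates: (0.277 × 9.798 − 1.344) / 0.657 = 2.086, power 98.2%.
- Illustrative smaller effect, 70.0% versus 48.4% (an assumption, not in the article): (0.216 × 9.798 − 1.362) / 0.678 = 1.112, power 86.7%.

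**Step 3. How much variance adjustment could remove.** The article gives no prognostic strength for either baseline value, so a range is assumed. Trials were simulated with 96 per arm, marginal rates 0.484 and 0.761, and two independent standard-normal covariates. The variance of the standardised (adjusted) risk difference was divided by that of the raw one. Ranges are over repeated sets of runs.

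| Log-odds per SD (two covariates) | Variance ratio, adjusted / raw |
|---|---|
| 0.3, 0.3 | 0.97 to 0.98 |
| 0.5, 0.5 | 0.91 to 0.92 |
| 0.5, 0.8 | 0.85 to 0.87 |
| 0.8, 1.0 | 0.77 to 0.83 |

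The reduction is therefore roughly 2% to 20%. The target difference stays at about 27 to 28 points. If the covariates predict nothing, adjustment costs about 1% in variance.

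**Step 4. What that means for power.** If a share R of the variance is removed, effective n = 96/(1 − R), which goes into the Step 2 formula.

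| R | Effective n per arm | Power, 76.1% vs 48.4% | Power, 70.0% vs 48.4% |
|---|---|---|---|
| 0 | 96 | 98.2% | 86.7% |
| 5% | 101.1 | 98.6% | 88.4% |
| 10% | 106.7 | 99.0% | 90.0% |
| 20% | 120 | 99.5% | 93.1% |

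For R of 5% to 20% the gain is 0.4 to 1.3 points on the stated rates and about 2 to 6 points at the smaller effect. Below 5% it is smaller still: at 3%, power at the smaller effect is 87.7%, a gain of 1 point.

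**Step 5. Check by direct simulation at 70.0% versus 48.4%** (3,000 trials per scenario). With odds ratios of 1.3, 1.5 and 2.0 per SD for each covariate, the chi-square test had 86% to 87% power throughout. Adjusted logistic regression had 87%, 89% and 92%. With equal rates of 48.4%, type I error was near 5% for both methods.

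**The case against.** The strongest reply is that nothing here is wrong. An unadjusted comparison in a 1:1 randomised trial is valid, and the simulations confirm its error rate. That stands.

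Three stronger readings are tempting, and the article supports none of them.

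- **Chance imbalance biases the result.** At 96 per arm the SE of a difference in baseline means is √(2/96) = 0.144 SD, so a gap of 0.2 SD or more in a given covariate arises in about 17% of trials. In simulation a gap of 0.2 SD moves the raw estimate by about 1 to 3 points. But this is random variation that the test's error rate already covers.
- **The whole plan ignores the baseline values.** A regression on shock resolution is planned. Its covariates could include them, and an article may leave that list to the full analysis plan. The point is therefore confined to the named primary test and to the unsuitable model type.
- **The trial is underpowered without adjustment.** On its own rates it is not.

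The size of the gain is also open to challenge. The top of the range needs odds ratios of about 2.2 and 2.7 per SD (e^0.8 and e^1.0) acting together. Baseline MAP is capped at 65 mmHg by the entry rule, and patients enrolled as soon as hypotension appears may cluster near that limit. This stands as a reason for caution. It does not remove the point: the cap is one-sided, and urine output has no entry limit. Simulating a skewed MAP with the same log-odds per SD gave ratios of 0.97 to 0.79, essentially unchanged.

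**Conclusion.** The point holds as an efficiency improvement to a stated method. The named primary test is valid but uses neither baseline component of its composite, and the accompanying beta regression is not a sound substitute.

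The loss is modest: roughly 2% to 20% of the variance of the risk difference. That is at most about 1 point of power on the planned rates, and about 2 to 6 points at 70.0% versus 48.4% once the variance reduction reaches 5% to 20%. These figures rest on assumed prognostic strengths, independent covariates and, in the second case, an assumed smaller effect. What does not depend on those assumptions is that the test is unadjusted, that both values are recorded, and that beta regression does not fit a yes/no outcome.

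**What to change.** Before any outcome data are analysed by arm, prespecify the primary estimate as a risk difference with 95% CI, standardised from a logistic model. The model contains arm, baseline MAP and baseline urine output (both continuous), the age and SOFA randomisation strata, and centre. It replaces the beta regression. Keep the chi-square or Fisher test as supportive.

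The cost is analysis-plan wording, with three details to settle:

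- **Baseline urine output.** The article lists baseline diuresis without a unit or collection window. Define it in ml/kg/h over a stated period.
- **Centre.** Eleven ICUs mean 10 centre terms, so 15 coefficients with arm (1), baseline values (2), age (1) and SOFA (1). On the planned rates about 192 × (1 − 0.6225) ≈ 72 failures are expected, just under 5 per coefficient. State in advance how small centres will be pooled, or use a random centre effect.
- **Software.** The plan names SPSS version 20. Whether it gives a standardised risk difference with CI directly was not checked; allow other software if it does not.
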